**Figure 1 F1:**
[figure not shown]
**Hypothermic reconditioning by gaseous O_2_-persufflation**. Above: Schematic representation of  the persufflated organ during cold storage on ice   Below: Detail of gas bubbles leaving a human liver through small pin-pricks set into post-sinusoidal venules.

The infrahepatic caval vein is temporarily closed by means of a small atraumatic bulldog clamp. After connecting the persufflation catheter to the gas tubing, postsinusoidal venules appear to be dilated due to the pressure applied to the hepatic venous system. Using a small 27 gauge syringe needle, small pinpricks are set into the dilated venules in all areas at the periphery of the liver lobes that allow the gas to leave the microvasculature.

After completion of the preparative procedures, sterile surgical gauze is soaked with the preservation solution and used to cover the liver during the time of persufflation.

Patients randomized to the control group receive a liver graft kept simply cold stored until implantation.

### Ethical considerations

The responsible physician will inform the patient about the background and present knowledge on the treatment protocol under study. It must be emphasized that the patient is allowed to refuse the treatment at any time prior to the operation. Before the patient is entered in the study the patient's written consent will be obtained. The principal investigator will ensure that this study will be carried out in agreement with the "Declaration of Helsinki [22] and local legal and regulatory requirements. The trial is monitored by the ZKS Essen according to Standard Operation Procedures (SOP) that are based on ICH-GCP guidelines.

An independent safety board monitors closely the proper conduct of the trial and all SAE reports to ensure the safety of the subjects during the course of the study.

The study has been approved by the institutional ethical review committee.

### Statistical analyses and data management

The primary endpoint is the maximum absolute AST value (U/l) on one of the first three post-operative days. As the AST distribution is highly skewed a non-parametric statistical procedure, the two-sided exact Mann-Whitney-U-test, is used for the confirmatory analysis. A SAS Macro will be used to estimate the relative effect *p *and to calculate 95% confidence intervals. Though missing data issues pertaining to the primary endpoint should be minimized given the continued monitoring during study conduct, the possibly remaining missing data of the primary endpoint will be replaced by the maximum global (across both groups) AST values mimicking a "worst-case scenario". The impact of other replacement or imputation strategies will be analyzed in sensitivity analyses.

The confirmatory analysis will be performed for the intention-to-treat population (full-analysis set) which includes all patients randomized for whom transplantation has been initiated.

In addition, to address the non-parametric Behrens-Fisher-problem (the sensitivity of the Mann-Whitney-U-test to any differences in distributions including differences in variances) and to integrate the stratum variable "MELD-Score", sensitivity analyses are preplanned using ANOVA statistics.

All secondary endpoints (see above) will be analyzed descriptively as described in the statistics analysis plan.

Data management and statistical analyses will be performed by the Center for Clinical Trials Essen (ZKSE).

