### Sample size calculation

The sample size calculation is performed for the primary endpoint (maximum absolute AST value during the first three days after transplantation) which is analyzed by an exact two-sided Mann-Whitney-U-test. Under the null hypothesis we expect no differences of the primary endpoint distributions for the two groups which translates into a relative effect *p *= 0.5, i.e. it is similarly likely to observe larger/smaller maximum AST values under one or the other group condition. Under the alternative hypotheses larger maximum AST values are on average expected for the standard treatment. For a significance level α = 0.05 (two-sided) and 52 patients per group would be necessary for a power of 0.8 to detect a relative effect of *p *= 0.66 (which is comparable to a mean difference of ~0.6 in units of standard deviations of a standard normal distribution if a parametric location shift (t-test) model would be appropriate). Considering a drop out rate of 10%, 58 patients per group (overall 116 patients) will be required.

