### Randomization and treatment

The randomization will be a stratified 1:1 stratified block randomization with blocks of variable block length with patient-level stratification factor Model for End-Stage Liver Disease (MELD) score (three levels: < 20, 20-30 und > 30). The donor liver is randomized by our study design. Only patients who had given informed consent to participate in the study will be included in the randomization and the study.

Randomization will be technically realized by a web-interface as organized by the Center for Clinical Trials Essen (ZKSE) who will also train the staff in running the software. Moreover, the ZKSE will monitor and control the randomization.

Treatment is restricted to the isolated liver graft after arrival in the transplantation clinic. In the treatment group, donor livers arriving at the hospital will be subjected to 2 hours of venous systemic oxygen persufflation (OP) prior to implantation, while still being stored in ice cold preservation solution as described previously [7,16,21].

In brief, medical grade oxygen gas is passed through a wash bottle and filtered through a membrane with pore size of 5 μm inserted into the inflow line. The filtered and humidified gas is then introduced into the liver by connecting the tubing to a catheter, previously inserted into the suprahepatic caval vein. In order to avoid any kind of barotraumas to the vulnerable hepatovasculature, The applied driving pressure of the gas entering the liver is limited to 18 mmHg, e.g. by means of an interposed pressure relief valve.

The liver is continuously placed immerged in cold preservation solution in a beaker, kept cold by surrounding crush ice (cf. Figure 1).

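### The confirmatory Mann-Whitney test ignores the MELD strata used in randomisation: it is valid and keeps its planned power, but is conservative and forgoes power if MELD predicts peak AST

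*Protocol article*

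**What the plan says.** Under Randomization and treatment, the protocol article sets 1:1 block randomisation with the "patient-level stratification factor Model for End-Stage Liver Disease (MELD) score" at three levels (below 20, 20 to 30, above 30). MELD is the only stratification factor it names.

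Under Statistical analyses and data management, it states that "a non-parametric statistical procedure, the two-sided exact Mann-Whitney-U-test, is used for the confirmatory analysis". The relative effect and its 95% confidence interval come from a SAS macro, again with no strata mentioned. MELD appears in the same section only in a supporting role: "to integrate the stratum variable 'MELD-Score', sensitivity analyses are preplanned using ANOVA statistics".

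The Sample size calculation section uses the same unstratified test for the primary endpoint, "which is analyzed by an exact two-sided Mann-Whitney-U-test".

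The article therefore names the confirmatory test and places MELD outside it. This is a stated choice, not a detail left to the statistical analysis plan.

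**The concern.** An exact Mann-Whitney p-value refers the observed rank sum to every reallocation of treatment labels across the whole trial. Blocks within MELD strata make many of those reallocations impossible, so the reference distribution is not the one that the randomisation generates.

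If MELD is related to peak AST, stratified blocks balance that part of the variation between the arms and largely remove it from the treatment contrast. The pooled test still counts it in its null variance. The test statistic then varies less than the test assumes, with three effects: the type I error falls below 5%, the interval for the relative effect covers more than 95%, and power that the design has made available goes unused.

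At stake is a near miss. If the pooled test fell just short of significance and a MELD-stratified analysis did not, the confirmatory conclusion would still rest on the less efficient test.

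**Working it through.** **Inputs from the protocol article.** Two-sided alpha is 0.05, with 52 per group for power 0.80 ("For a significance level α = 0.05 (two-sided) and 52 patients per group would be necessary for a power of 0.8"), relative effect 0.66 ("to detect a relative effect of *p *= 0.66") against 0.5 under the null, and 58 per group after 10% dropout ("Considering a drop out rate of 10%, 58 patients per group (overall 116 patients) will be required"). Allocation is 1:1 in blocks within three MELD levels.

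**Inputs assumed, because the documents do not give them.** R², the share of AST variation explained by MELD on a normal latent scale, is varied from 0 to 0.30. Stratum shares are 50/30/20%. Blocks are of 4 or 6 (the article says only that block length varies). Rank tests are unchanged by monotone transformation, so a normal scale is adequate for skewed AST.

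**Step 1: the plan's own figure.** Noether's formula for the pooled test gives N = (1.960 + 0.842)² / [12 × 0.25 × (0.66 − 0.5)²] = 7.849 / 0.0768 = 102.2, hence 52 per group. Then 52 / 0.90 = 57.8, hence 58 per group and 116 in total. Both match. Power at 104 patients is Φ(√(3 × 104) × 0.16 − 1.960) = Φ(0.866) = 80.7%. The equivalent shift is √2 × Φ⁻¹(0.66) = 0.583 SD, in line with the article's remark, "which is comparable to a mean difference of ~0.6 in units of standard deviations of a standard normal distribution".

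**Step 2: type I error of the pooled test.** Stratified blocks reduce the true variance of the contrast by about the factor 1 − R², so the type I error is about 2[1 − Φ(1.96 / √(1 − R²))]. At R² = 0.10, 0.20 and 0.30 this gives 3.9%, 2.8% and 1.9%.

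**Step 3: within-stratum relative effect.** With the marginal value held at 0.66, the within-stratum value is Φ(0.583 / √(2(1 − R²))). At R² = 0.10, 0.20 and 0.30 this gives 0.67, 0.68 and 0.69.

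**Step 4: simulation.** 104 patients, 8,000 trials per setting, pooled Mann-Whitney against van Elteren:

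| R² | Power, pooled | Power, stratified | Change (points) | Type I error, pooled |
|---|---|---|---|---|
| 0 | 82.4% | 81.4% | −1.0 | 5.2% |
| 0.05 | 82.3% | 83.0% | +0.7 | 4.8% |
| 0.10 | 83.2% | 85.2% | +2.0 | 4.1% |
| 0.20 | 84.4% | 88.8% | +4.4 | 2.7% |
| 0.30 | 84.9% | 92.0% | +7.1 | 2.0% |

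Simulation error (one standard error at 8,000 trials) is about 0.4 points for a power near 82% and 0.2 points for a rate near 5%, so 5.2% at R² = 0 is not an excess.

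**Step 5: a second split.** With shares of 45/35/20% and 10,000 trials, the power changes are −0.6, +0.7, +1.6, +5.0 and +6.9 points at the same R² values. At R² = 0.02 the two tests are level (81.7% against 81.6%). The stratified test's type I error stays between 4.8% and 5.1%. Coverage of an unstratified 95% interval for the relative effect under the null is 94.7, 95.1, 96.1, 96.9 and 97.9%.

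**The case against.** The strongest reply is that design and analysis already agree: the trial was sized for the same pooled test that it will use, and that test keeps at least 80% power in every setting above. This stands. A reader might infer from the mismatch that the trial is underpowered, but the sample size section reproduces and the power forgone is extra to the plan.

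A reader might also infer that error control or the interval is unsound. The documents do not support that. Under stratified randomisation the departure runs only in the safe direction: type I error at or below 5% and coverage at or above 95%, within simulation error.

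Nor is it clear that MELD matters much for this endpoint. MELD describes the recipient, whereas peak AST is chosen as a surrogate of graft reperfusion injury, and the Background section dwells on donor age, graft fat and preservation. A weak association is plausible, and at R² of 0.05 or less the gain is under 1 point. This limits the size of the point. Against it, MELD is the only factor on which the trial chose to stratify, which makes most sense if it was thought prognostic.

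MELD is also not ignored, since sensitivity analyses that include it are preplanned. But these do not carry the confirmatory decision or, as written, the headline estimate and interval.

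Lastly, a stratum-weighted relative effect is not the same quantity as the marginal 0.66. That is correct, and it is a real cost of the change.

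**Conclusion.** The point holds as one of efficiency, not of error control. The confirmatory test and, as written, the relative effect with its interval do not follow the stratified randomisation. The pooled test remains valid and keeps its planned power, so a significant result from it could be trusted.

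The cost depends on an association that the documents do not state. The gain from stratifying is negligible if MELD explains about 5% of AST variation or less, about 2 points of power at 10%, 4 to 5 at 20% and 7 at 30%. Over 10 to 30%, the pooled test runs at a true type I error of about 4% down to 2%. These figures rest on 104 analysed patients, the assumed stratum shares, a normal latent scale and a constant shift across strata. The two splits tried give similar results.

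The trade is lopsided in favour of stratifying: about 1 point of power at risk against as much as 7 to gain. In a trial of 116 patients planned at 80% power, that makes the change worthwhile.

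**What to change.** Before unblinding, amend the protocol and the statistical analysis plan as follows:

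- Make the MELD-stratified Wilcoxon (van Elteren) test the two-sided confirmatory test, with its p-value from permutation within the three randomisation strata.
- Report a stratum-weighted relative effect with its 95% confidence interval as the main estimate.
- Keep the pooled exact Mann-Whitney test and the marginal relative effect as sensitivity analyses.
- State next to the sample size that the reported effect is now a within-stratum one. Under the assumed models it would be about 0.67 to 0.69 where the marginal value is 0.66 and R² is 10 to 30%.

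No further patients or data are needed and the sample size need not change. The costs are about 1 point of power if MELD is unrelated to peak AST, and the rewording of the effect measure.

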### Adverse events

Any unexpected clinical adverse event or abnormal laboratory test value that is serious, including death, occurring during the course of the study must be reported by the study coordinator [name] (Bonn) within 7 days using the Serious Adverse Event form. The investigator at the site Essen and [name] have to assess, if this SAE was (likely to be) caused by the transplantation and/or oxygen persufflation. This SAE will be sent to the IEC by [name]. The Data Safety Monitoring Board (DSMB) of OPAL will receive a list of SAE and complication twice a year. Cases of death will reported without delay to the DSMB.

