### Main exclusion criteria

Patients presenting with any of the following are not included in the trial:

• Listed as high urgency (HU)

• Participation in this study at an earlier time

• Simultaneous participation in other clinical trial

• Positive test for HIV

• Pregnant or nursing

All patients are observed for seven days following transplantation on a daily basis. Follow up includes additional observations on the day of discharge and 3 month after transplantation. Patients are followed until 3 month after the last patient is randomized for this trial and are asked to attend clinical routine follow up subsequent to termination of the study.

The schedule for study related activities and data collection is listed in table 1.

**Table 1 T1:** Flow chart

	screening	waiting- phase	preoperative	OP	postoperative								follow up (3 month)
						
					D 1		D3	D3	D4	D5	D6	discharge	
Informed consent	X												
In-/ex-clusion criteria	X		X										
Demography	X												
Medical history	X												
Randomisation			X										
BQS/complications			X	X								X	X
Postoperative dialysis					X	X	X	X	X	X	X	X	
Time of mechanical ventilation					X	X	X	X	X	X	X	X	
Laboratory parameters	X		X		X	X	X	X	X	X	X	X	X
SAE			X	X	X	X	X	X	X	X	X	X	
Death				X	X	X	X	X	X	X	X	X	X
Retransplantation					X	X	X	X	X	X	X	X	X

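### The SAE form is required only for unexpected serious events, and Table 1 ends SAE collection at discharge although the text covers the whole study

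*Protocol article*

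**What the plan says.** Three parts of the protocol article bear on this.

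- **Adverse events.** The duty to file a form applies to "Any unexpected clinical adverse event or abnormal laboratory test value that is serious, including death, occurring during the course of the study". The form is due within 7 days. The investigator and the study coordinator then judge whether transplantation and/or persufflation caused the event, and the report goes to the IEC. Separately, the safety board gets a half-yearly list of SAEs and complications, and is told of deaths immediately.
- **Follow-up text (under Main exclusion criteria).** "Follow up includes additional observations on the day of discharge and 3 month after transplantation". In addition, "Patients are followed until 3 month after the last patient is randomized for this trial", so patients randomised early are followed beyond their own 3-month visit.
- **Table 1 (same section).** The text makes this table the schedule: "The schedule for study related activities and data collection is listed in table 1". Its SAE row is marked from the preoperative visit to discharge and is empty in the last column, the 3-month follow-up.

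**The concern.** Expectedness normally decides which serious events are reported urgently. It does not normally decide which ones are recorded as serious. Here it sits in the recording rule. The protocol itself treats the main harms in this population as foreseeable: the Background says that marginal grafts carry a raised risk of dysfunction or non-function, and Objectives and endpoints lists death, retransplantation, haemodialysis and complications as outcomes in advance.

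A harm from persufflation need not be a new kind of event. It could be an excess of familiar post-transplant events in one arm. The only causality step that the article describes is the one tied to the SAE form. The Discussion also defends leaving sham pinpricks out of the control arm partly because side effects can then be attributed more easily to the treated arm. A filing rule that leaves out foreseeable events, and a schedule that stops at discharge, both weaken that attribution.

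**Working it through.** There is no figure to recompute. The check is a reading of the texts side by side and a count of marks in Table 1.

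**Step 1: the filing rule.** The sentence in Adverse events sets three conditions: the event is unexpected, it is serious, and it occurs during the study. An event that is serious and occurs during the study but was expected fails the first condition. No form is then required, and the 7-day report, the causality judgement and the forwarding to the IEC, which all follow from the form, are not triggered.

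**Step 2: the window in Table 1.** The SAE row reads "SAE X X X X X X X X X X". Set against the column headers:

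| Row | Marks | First mark | Last mark | 3-month follow-up |
|---|---|---|---|---|
| SAE | 10 = preoperative 1 + OP 1 + daily columns 7 + discharge 1 | preoperative | discharge | empty |
| Death | 10 = OP 1 + daily columns 7 + discharge 1 + follow-up 1 | OP | follow-up | marked |
| Retransplantation | 9 = daily columns 7 + discharge 1 + follow-up 1 | first daily column | follow-up | marked |
| BQS/complications | 4 = preoperative 1 + OP 1 + discharge 1 + follow-up 1 | preoperative | follow-up | marked |

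Laboratory parameters are also marked at follow-up. The garbled day labels in the header do not matter here: the last column is plainly in use for other rows and empty for SAEs.

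**Step 3: text against table.** The text applies the duty throughout the study, and the study includes a 3-month visit and, for early patients, later follow-up. The table stops at discharge. The two therefore disagree on the interval from discharge to at least 3 months, for every one of the planned 116 patients who reaches discharge.

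**Step 4: what is caught elsewhere.** Deaths, retransplantations and BQS/complications are collected at 3 months. Death, retransplantation and complication rate are also secondary outcomes. The safety board's half-yearly list covers complications as well as SAEs, and the immediate notice of deaths carries no expectedness limit.

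**Step 5: what is left.** Two things remain:

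- Expected serious events of any kind lose the 7-day report, the causality judgement and the forwarding to the IEC, even where the event itself is counted as an outcome.
- After discharge, on the table's schedule, the same applies to non-fatal serious events. Those that are neither a retransplantation nor covered by BQS/complications may not be collected at the 3-month visit at all.

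**The case against.** The strongest reply is that the practical loss is small and the wording only loose. Several parts of it stand.

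- **The board.** A reader might infer that the article contradicts itself by promising the board every SAE. It does not. Ethical considerations says that the board "monitors closely the proper conduct of the trial and all SAE reports", which means the reports that are filed. That is compatible with a narrow filing rule. Nor would the board be blind to foreseeable harms, since it also receives complications and death notices.
- **After discharge.** A reader might infer that no SAE data will exist after discharge. That is not established. The duty in Adverse events is triggered by the event, not by a visit, and an empty visit cell does not cancel it. What can be said is that table and text differ.
- **Which events are expected.** The article gives no list, so it cannot be said as fact that non-function or surgical complications fall outside the rule. Asking whether transplantation was the cause suggests that transplant-related events were meant to be filed. The word may be a slip.
- **Condensed format.** A full protocol may define SAE handling in more detail.

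The last two points do not remove the finding. If the word is a slip, correcting it is the remedy. The concern is with what the article states rather than with missing detail, and fuller text elsewhere would not make the printed sentence and the printed table agree. The layout of the board's list is not stated wrongly anywhere, so nothing follows about it.

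**Conclusion.** The point holds in a limited form. As written, the filing rule excludes serious but expected events, and Table 1 and the text disagree on whether SAEs are collected after discharge. The conclusion on the filing rule assumes a literal reading of the word unexpected. The conclusion on the window assumes that sites use Table 1 as their collection schedule, as the text presents it.

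The gap is partial, and its size cannot be determined from the article: there is no list of expected events, no definition of BQS/complications and no event rate. It concerns the capture and causal assessment of harms. It does not touch the primary endpoint or its analysis.

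**What to change.** - In Adverse events, delete the word unexpected from the recording rule, so that every serious event gets a form. Use expectedness only to decide which reports are expedited.
- In Table 1, mark the SAE row at the 3-month follow-up, so that the schedule matches the text. Because early patients are followed past that visit, the same sentence in Adverse events should say when the SAE window closes.

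The cost is one word, one table cell and a short clause, plus somewhat more SAE forms and causality judgements. No visit is added, since the 3-month visit already takes place and already collects complications, deaths and retransplantations.
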